### Data management and analysis

All analyses will be conducted on an intention to treat basis. The outcomes measured at 6, 12, 24 and 52 weeks will be analysed using linear mixed and logistic regression models that will include their respective baseline scores as a covariate, subjects as a random effect and treatment conditions as fixed factors. Age, gender, duration of condition and IES scores will be included as covariates in the analysis. Regression diagnostics will be used to check for normality of the measures and homogeneity of variance as appropriate. Alpha will be set at 0.01.

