**Method/Design:**

A double-blind randomised controlled trial will be conducted. 120 participants with chronic whiplash, grade II will be randomised to receive either 1) dry-needling, advice and exercise or 2) sham dry-needling, advice and exercise. All participants will receive an educational booklet on whiplash. Participants who are randomised to Group 1 will receive 6 treatments of combined dry-needling and exercise delivered in the first 3 weeks of the 6 week program, and 4 treatments of exercise only in the last 3 weeks of the program. Participants randomised to Group 2 will receive an identical protocol, except that a sham dry-needling technique will be used instead of dry-needling. The primary outcome measures are the Neck Disability Index (NDI) and participants' perceived recovery. Outcomes will be measured at 6, 12, 24 and 52 weeks after randomization by an assessor who is blind to the group allocation of the participants. In parallel, an economic analysis will be conducted.

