### Outcome Measures

Age, gender, time since injury, compensation status, previous treatments and medication usage for the whiplash condition will be obtained at baseline. The assessor administering the outcomes will be blind to the group allocation of the participant. Outcome measures will be assessed at baseline, 6, 12, 24 and 52 weeks after randomization.

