### Primary outcome measures

1. Neck-specific measure of disability (Neck Disability Index)[20]

2. Patient's global impression of recovery (-5 to +5 scale) [21]

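### Two primary outcomes at four unranked visits with a flat alpha of 0.01: the threshold fits neither reading of the analysis and costs power in a trial sized at 0.05

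*Protocol article*

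**What the plan says.** The Abstract of the protocol article states: "The primary outcome measures are the Neck Disability Index (NDI) and participants' perceived recovery". The section Primary outcome measures lists the same two, "Neck-specific measure of disability (Neck Disability Index" and "Patient's global impression of recovery (-5 to +5 scale", without ranking one above the other.

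The section Outcome Measures sets the schedule: "Outcome measures will be assessed at baseline, 6, 12, 24 and 52 weeks after randomization". The section Data management and analysis carries all four follow-up visits into the analysis on equal terms: "The outcomes measured at 6, 12, 24 and 52 weeks will be analysed using linear mixed and logistic regression models". The model is described as having "subjects as a random effect and treatment conditions as fixed factors", plus baseline and other covariates. No visit term and no treatment-by-visit term is named. The section closes with "Alpha will be set at 0.01" and does not say whether this is per test or overall, or why 0.01 was chosen.

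The section Sample size calculations uses the NDI alone, at no named visit: a 7-point difference, SD 18, 80% power and p = 0.05. It arrives at 54 per group, raised to 60 for 10% loss to follow-up.

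**The concern.** The article fixes an outcome-by-visit structure and a threshold, and the two do not match. Nothing in it says which comparison answers the trial's main question, or whether one or both primary outcomes must be positive. On this document alone, a positive claim could rest on either outcome at any visit.

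The threshold does not settle the matter. As a correction for eight comparisons, 0.01 is too loose to guarantee 5% overall. As a correction for two, it is stricter than needed. Either way it is five times smaller than the alpha behind the sample size, so a real NDI effect of the size the trial was planned for is more likely to be missed than the stated 80% power suggests.

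**Working it through.** **Inputs from the protocol article.** Two primary outcomes (Primary outcome measures); four follow-up visits (Outcome Measures); analysis alpha 0.01 (Data management and analysis); 7 points, SD 18, alpha 0.05, 80% power, 54 evaluable per group (Sample size calculations).

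**Assumed, because the article does not give them.** Two-sided tests; correlations between visits and between outcomes; the correlation between baseline and follow-up NDI.

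**1. The plan's own figure.** For two means, n per group = 2 × [SD × (z for alpha/2 + z for power) / difference]².
- With 7, 18, 0.05 and 80%: 2 × [18 × (1.960 + 0.842) / 7]² = 103.8, so 104 per group. The stated 54 is not reproduced.
- The dropout step is reproduced: 54 / 0.9 = 60.
- If baseline adjustment is credited, the SD becomes 18 × √(1 − r²). At r = 0.70 this is 12.86, and a t-test with 54 per group at 0.05 has 80.1% power. So r = 0.70 is the assumption under which the stated 80% holds.

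Whether 54 is right is a separate matter. Power is therefore shown both ways below.

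**2. Overall error if each outcome is tested at each visit.** 2 × 4 = 8 tests at 0.01.
- Upper bound under any correlation: 8 × 0.01 = 8.0%.
- Independent tests: 1 − 0.99⁸ = 7.7%.
- Simulated correlated normal statistics (2 million draws). In the first five rows the correlation between different outcomes at different visits is the product of the two values shown:

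| Between visits | Between outcomes | Chance of at least one false positive |
|---|---|---|
| 0.3 | 0.3 | 7.3% |
| 0.5 | 0.5 | 6.5% |
| 0.7 | 0.7 | 5.1% |
| 0.8 | 0.7 | 4.5% |
| 0.8 | 0.8 | 4.2% |
| every pair 0.5 | every pair 0.5 | 6.1% |

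A guaranteed 5% over eight tests needs 0.05 / 8 = 0.00625. A threshold of 0.01 guarantees it for at most five tests (5 × 0.01 = 0.05).

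**3. Overall error if there is one treatment test per outcome.** 2 × 0.01 = 2.0% at most. A 5% budget split evenly over two tests would allow 0.025 each.

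**4. NDI power at 54 per group, 7 points (two-sample t-test).**

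| Two-sided alpha | SD 18, unadjusted | SD 12.86 (r = 0.70 assumed) |
|---|---|---|
| 0.05 (used for sizing) | 52% | 80% |
| 0.025 | 40% | 71% |
| 0.01 (stated for analysis) | 28% | 58% |

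A check that needs no value of r: accept 80% at 0.05 as given and use the normal approximation. The expected z statistic is 1.960 + 0.842 = 2.802. Against the 0.01 critical value of 2.576, power is Φ(2.802 − 2.576) = 59%. Restoring 80% at 0.01 would take 54 × [(2.576 + 0.842) / 2.802]² = 80.4, so 81 evaluable per group.

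**The case against.** Four points can be made for the plan.

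- **Eight tests is a reading, not a count in the text.** The model as described could yield one treatment effect per outcome across all visits, and then overall error is at most 2%. This stands. It removes the error concern on that reading but makes 0.01 needlessly strict, so the threshold is still poorly matched.
- **A stricter alpha is a legitimate, cautious response to several outcomes and visits.** That is fair as a principle, and the article does not say that 0.01 was meant as a formal correction. But caution in the analysis has to be carried into the sample size, and here it was not.
- **A condensed article may leave the primary visit and success rule to the full protocol or analysis plan.** This also stands: their absence here does not show that no rule exists, and would not be a finding alone. What remains is what the article itself states: two primary outcomes, four unranked visits, analysis at 0.01 and sizing at 0.05.
- **The excess over 5% is modest and rests on assumed correlations.** Correct. A reader might infer that the plan's overall error exceeds 5%. The documents do not support that: they give no correlations, and strong ones (0.8 between visits with 0.7 or 0.8 between outcomes) bring it below 5%. The defensible statement is that 5% is not guaranteed.

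A reader might also infer that the low unadjusted power comes from the 0.01 threshold alone. It does not: at 0.05 the stated inputs already give only 52%, because 54 per group does not follow from 7 and 18.

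**Conclusion.** The concern holds in a limited form. The article identifies no primary contrast, and its alpha of 0.01 fits neither plausible reading of its analysis section: it does not guarantee 5% over eight tests, and it underspends the error budget over two.

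The firmest part is the mismatch between sizing at 0.05 and testing at 0.01. It costs about 22 percentage points of NDI power if the stated 80% is accepted (to 58%, with r = 0.70 assumed), or about 24 points from the stated inputs unadjusted (52% to 28%). These figures assume two-sided tests and a single NDI comparison.

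The error side is weaker, since it depends on the per-visit reading and on correlations that the article does not give. This should be corrected, but it does not invalidate the design.

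**What to change.** Before unblinding:

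1. Name one primary visit, or define one overall treatment contrast per outcome across the visits. The sponsor should choose and justify it; the article favours no visit over another.
2. Test the NDI and perceived recovery on that contrast with Holm or Hochberg at two-sided 0.05 overall, and state that success needs at least one of the two. Holm holds the overall error under any correlation; Hochberg relies on the two tests not being negatively dependent.
3. Report the remaining visits as secondary, with confidence intervals.
4. Restate the power at the threshold actually used. At 0.025, the stricter of the two steps, NDI power at 54 per group is 71% with r = 0.70 assumed (58% at 0.01), or 40% unadjusted (28% at 0.01). Both remain below the stated 80%.

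The cost is plan wording only, with no added participants. The downside is that effects at visits outside the primary contrast become supportive, not confirmatory.

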### Sample size calculations

The NDI was used to determine sample size, as previous clinical trials have shown this variable to have a smaller effect size than the measure of perceived recovery [5]. The minimal clinically important change for the NDI is 7 points [26] with a conservative standard deviation of 18 based on previous work[5,27]. Based on 80% power at *p *= 0.05, 54 participants will be required in each group. Allowing for a 10% loss to follow up, a total of 60 participants will be required in each group, with 120 participants in total.

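### The sample size rests on 80% power at p = 0.05, but the analysis section sets alpha at 0.01 without naming outcomes, so the stated power does not apply to a test at 0.01

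*Protocol article*

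**What the plan says.** Protocol article, Sample size calculations: "The NDI was used to determine sample size". The inputs are a difference of 7 points ("The minimal clinically important change for the NDI is 7 points") and an SD of 18 ("with a conservative standard deviation of 18 based on previous work"). The section opens its result with "Based on 80% power" and gives the significance level and the answer as "0.05, 54 participants will be required in each group". After an allowance for 10% loss it reaches "a total of 60 participants will be required in each group, with 120 participants in total". Whether the test is one- or two-sided is not stated.

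Protocol article, Primary outcome measures: the NDI is one of two primary outcomes, the other being global impression of recovery.

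Protocol article, Data management and analysis: outcomes at the four follow-up times are to be analysed by linear mixed and logistic models with the baseline score as a covariate. The section ends "Alpha will be set at 0.01". That sentence names no outcome, time point or analysis, and gives no reason such as multiplicity.

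**The concern.** The two sections give different significance levels, and the later one is unqualified. Read naturally, it covers the NDI. Power is a property of a particular test at a particular level, so a figure computed at 0.05 cannot be carried over to a test at 0.01.

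Two things are at stake. First, an NDI p-value between 0.01 and 0.05 would count as significant by the level used for sizing and not by the level set for analysis. If this is still open when results are seen, the threshold can be chosen after the fact. Second, a non-significant NDI result would be read against 80% power that the trial does not have at 0.01.

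**Working it through.** **Inputs.** From Sample size calculations: difference 7, SD 18, 80% power, level 0.05, 54 evaluable and 60 randomised per group. From Data management and analysis: level 0.01. Two-sided tests and 1:1 allocation are taken as the base case. Power figures are from the two-sample t-test; the normal approximation, shown alongside, lies within about one percentage point.

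**1. The plan's own figure.** The two-group formula is n per group = 2·SD²·(z₁₋α/₂ + z₀.₈₀)² / difference². At 0.05 this gives 2·324·(1.960 + 0.842)² / 49 = 103.8, or 104 per group (105 by the t-test), not 54. A one-sided test would need 82 (83 by the t-test). The stated 54 matches a one-sample or paired t-test with the same inputs (53.9). The loss allowance is right: 54 / 0.90 = 60. The gap between 54 and 105 is a separate error, and steps 2 and 3 keep it apart from the change in alpha.

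**2. Effect of alpha alone, taking 54 per group as giving 80% at two-sided 0.05.** The standardised effect on the z scale is then 1.960 + 0.842 = 2.802. At 0.01 the critical value is 2.576, so power = Φ(2.802 − 2.576) = Φ(0.226) = 0.589. The t-test gives 0.582, about **58%**. The number needed for 80% at 0.01 is 54 × [(2.576 + 0.842) / (1.960 + 0.842)]² = 54 × 1.488 = 80.4, or **81 evaluable per group** (80.6 by the t-test). With 10% loss that is 81 / 0.90 = 90 per group. This step needs neither the SD nor a baseline correlation.

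**3. On the stated inputs, unadjusted.** The standard error of the difference at 54 per group is 18·√(2/54) = 3.464, and 7 / 3.464 = 2.021.

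| Level (two-sided) | Normal approximation | t-test, 54 per group | t-test, 60 per group |
|---|---|---|---|
| 0.05 | Φ(2.021 − 1.960) = 0.524 | **52%** | 56% |
| 0.01 | Φ(2.021 − 2.576) = 0.289 | **28%** | 32% |

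The difference detectable with 80% power at 0.01 and 54 per group is (2.576 + 0.842) × 3.464 = 11.8 points, or **12.0** by the t-test, against the 7 points used for sizing. Reaching 80% at 0.01 on these inputs would take 156.1, that is 157 per group. That last figure contains both the sample-size error and the change in alpha.

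**4. Baseline adjustment.** The planned model adjusts for baseline, which reduces the SD to 18·√(1 − r²). The article gives no r, so these values are assumptions (54 per group, two-sided t-test):

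| Assumed r | Adjusted SD | Power at 0.05 | Power at 0.01 |
|---|---|---|---|
| 0.5 | 15.6 | 64% | 39% |
| 0.7 | 12.9 | 80% | 58% |
| 0.8 | 10.8 | 92% | 77% |

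The correlation that would make 54 right at 0.05 (about 0.7) again gives 58% at 0.01. A correlation high enough for 80% at 0.01 (just above 0.81) would have given about 93% at 0.05, not the stated 80%.

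**5. One-sided reading.** Unadjusted one-sided power at 54 per group is 64% at 0.05 and 37% at 0.01, so this does not reconcile the two sections either.

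**The case against.** The strongest reply concerns scope. The phrase about all analyses in Data management and analysis governs intention to treat; the alpha sentence stands alone and names nothing. It may have been meant for the secondary outcomes, or as an allowance for two primaries and four follow-up times. A reader might infer that 0.01 is definitely the level for the NDI. That is the natural reading, but the article does not say it, so the supportable statement is that 0.01 is unscoped and unreconciled with 0.05. This does not remove the conflict: if the stricter level was a multiplicity allowance covering the NDI, the sample size had to use it.

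The second reply concerns size. A reader might take 28% as the cost of the stricter alpha, or conclude that a true 7-point benefit would most likely be missed. Neither is supported. The 28% includes the separate sample-size error, since power on the stated inputs is already 52% at 0.05. The planned model also adjusts for baseline: at an assumed r of 0.7 power at 0.01 is 58%, so detection is more likely than not. Repeated measures in the mixed model might add precision, and this is not quantified here.

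The third reply is that a strict alpha is a defensible choice with two primaries and four time points. That stands. The fault is the mismatch, and the documents give no ground for calling 0.05 the correct level.

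**Conclusion.** The contradiction is real and is wrong as written: 80% power at 0.05 does not apply to a test at 0.01. The part due to alpha alone is a fall from 80% to about 58% if 54 per group is taken at face value, or from 52% to 28% on the stated difference and SD without adjustment. These figures assume two-sided tests, 54 evaluable per group and, in the second case, no gain from baseline adjustment or repeated measures. The point stands apart from the error in the 54: correcting that number at 0.05 would leave the two levels in conflict. How much power the planned model would have at 0.01 cannot be settled from the article, because the baseline correlation is not given.

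**What to change.** Before unblinding, state one alpha for the primary analysis, with its sidedness, and use it in both Sample size calculations and Data management and analysis.

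- If 0.01 is kept for the primary outcomes, restate the power and the detectable difference in Sample size calculations at 0.01, with any baseline correlation assumed.
- If 0.01 was meant only for secondary outcomes, say so in Data management and analysis, and state power at the alpha actually applied to the NDI. If an overall 0.05 is split between the two primaries, that level is again not 0.05. With an even split (0.025), power at 54 per group is 40% unadjusted, or 71% at an assumed r of 0.7.

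The cost is a sentence or two, with no added participants. The downside is a stated power less favourable than 80%.

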### Data integrity

The integrity of trial data will be monitored by regularly scrutinising data sheets for omissions and errors. Data will be double-entered and the source of any inconsistencies will be explored and resolved.

## Discussion

Although many people experience rapid recovery from pain and disability associated with whiplash within the first three months, a significant proportion can have ongoing mild to moderate pain and disability[28]. It has been shown that the presence of widespread sensory hypersensitivity indicative of augmented pain processing mechanisms is associated with higher levels of pain, disability and poor functional recovery following whiplash injury [29]. Chronic patients with these features have been shown to have a poor response to an exercise-based intervention approach[5]. In order to enhance the treatment outcomes of an exercise intervention, an additional modality or technique could be used in conjunction with an exercise programme to address the sensory hypersensitivity of whiplash. Modalities such as dry needling and acupuncture are commonly used in the treatment of musculoskeletal pain conditions[12], although the benefit of dry needling for the treatment of whiplash is not yet known. Therefore, this trial aims to investigate whether the addition of dry needling to an exercise programme will reduce pain and disability of chronic whiplash.

The exercise programme received by all participants in the trial includes specific exercises to re-educate cervical and scapular muscle control endurance and strength and are of low-load in nature. These exercises are tailored to the ability of the participants by the trial physiotherapists. This type of exercise programme has previously shown modest effects in the treatment of chronic whiplash by reducing pain and disability [4,5] and was therefore the programme of choice for this trial.

A sham dry needling intervention will be used as a in the comparison group to assess the effects of dry-needling on whiplash. Sham dry needling invokes a similar sensation to that produced by true dry-needling, without the needle entering the skin. This technique is proposed to have a lesser physiological effect than true needling [19]. Application of the sham and true dry needles are to the posterior cervical and thoracic spine whilst the participant is prone, which will allow participant blinding to their group allocation. A blinded independent trial assessor will conduct participant assessments. The methodology of this double-blind randomised controlled trial meets the CONSORT statement and guidelines [30].

An economic evaluation of the dry-needling, advice and graded exercise approach will also be conducted as a secondary aim in this trial. As the economic cost of whiplash injury is extensive, developing effective treatment programmes which minimise pain, disability and resultant economic cost is desirable.

It is hypothesised that the dry needling approach will decrease the pain and disability of chronic whiplash by reducing the sensory hypersensitivity and facilitate the effects of the exercise program. The study outcomes will facilitate the development of effective treatment plans for chronic pain and disability following a whiplash injury and have the potential to reduce the economic burden of this condition.
